### The Secondary Aims

• To identify the potential biomarkers for IMN population and/or subgroup population with specific characteristics.• To investigate the relationship between population characteristics including Chinese medicine syndromes and tongue features in IMN patients and clinical outcomes.

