### Eligibility Criteria

Eligible candidates for the study are IMN patients of any risk levels to capture a broad spectrum of clinical presentations. Inclusion criteria include Chinese adults aged from 18 to 85 years old; diagnosis of biopsy-proven IMN or antibodies against phospholipase A2 receptor (PLA2R)-positive patients who are not associated with other diseases which cause secondary MN, such as systemic lupus erythematous, infections with hepatitis B virus, hepatitis C virus, or syphilis, sarcoidosis, and cancer. Patients with the following criteria will be excluded: patients with a GFR less than 15 ml/min/1.73 m^2^; patients with comorbidities including malignant cancers, decompensated cirrhosis, hematologic diseases, and mental diseases.

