The data of the core Chinese medicine syndrome of dampness in IMN will be collected by using the validated Dampness Syndrome Scale (Lu et al., 2021) and the tongue image acquisition system. The scale consists of 30 items. There are five options for each item from 0 to 4 which indicate no symptoms, mild, moderate, heavy, and very heavy symptoms. The total score ranges from 0 to 120. More than 15 items with at least one point can be defined as dampness syndrome. The higher the score, the more severe the dampness syndrome. Tongue images will be captured by using a smartphone tongue image acquisition application with a standard color correction chart (Figure 2) and quantified the tongue characteristic by using a computerized tongue image analysis system (Shanghai Daosh Medical Technology Co., Ltd.). (ISO, 2019; ISO/TS, 2020).

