### Statistical Plan

Attempting to ensure equivalence in baseline characteristics of participants between the CHM group and the conventional therapy group, a propensity score method will be performed. Variables involving age, sex, proteinuria, eGFR, serum albumin, uric acid, PLA2R antibody level, and pathological type will be included into the logistic regression model to calculate a propensity score for each participant. Participants who are exposed to CHM will be matched to those who receive conventional drugs alone based on the propensity score, using the greedy matching with a standard calliper width of 0.2 and without case replacement. Covariate balance of the matched cohort will be assessed using the mean standardized differences. When a |d| > 0.10, it is considered as an imbalance. Inverse probability of treatment weighting based on the propensity score will also be performed to evaluate the robustness of the matching results.

Baseline demographic variables will be presented as means, medians, or percentages, and using Chi-square test, independent t test, or Mann-Whitney *U* test, as appropriate. Outcomes of composite remission, CR, PR, no response, death, relapse, and composite endpoint will be analysed by using Chi-square test and logistic regression. Odd ratios and 95% confidence intervals will be estimated. Time to remission will be analysed by using Cox regression model, adjusting for gender, age, baseline proteinuria, GFR, PLA2R antibody level, uric acid, Chinese medicine syndrome, and propensity score.

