Subgroup analysis will be performed on age, gender, diagnosis criteria (i.e., biopsy proven or anti-PLA2R positive), PLA2R positive or negative, blood lipid levels, different risk levels of progressive loss of kidney function, “incident patient” and “prevalent patient”, Chinese medicine syndromes, different assay methods for serum creatinine and proteinuria, different levels of CHM exposure, treatment regimens (CHM alone, conventional medication alone and the combination), conventional medications, and CHM with and without immunosuppressive effect. For the analyses of Chinese medicine syndromes, besides Chi-square test between groups of patients with and without dampness syndrome, a trend test will be performed to assess the dose-response relationship between dampness syndrome and clinical outcomes. CHM with immunosuppressive effect will be defined as either herbal formulas or proprietary CHM products which contain either *Tripterygium wilfordii* Hook. f, *Tripterygium hypoglaucum* (Levl.) Hutch and *Sinomenium acutum* (Thumb.) Rehd. et Wils (Menispermaceae, SA) or their compounds (Zhao et al., 2012; Chen et al., 2014; Pei et al., 2016; Lv et al., 2019; Zheng et al., 2019).

GFR will be estimated by 2009 CKD-EPI creatinine equation and 2021 CKD-EPI creatinine-cystatin C equation. As the 2021 equation has not yet been validated in the Chinese population, analyses involved eGFR will use the estimates calculated by the 2009 equation, and sensitivity analyses based on the 2021 equation will be performed. To eliminate the acute effect, incident patients who experience a serum creatinine increase of more than 30% within 12 weeks after initiated treatments will be excluded in analyses on endpoints in terms of ESRD, 40% eGFR reduction, and eGFR slope.

Additionally, in order to assess the risk of performance bias, the change of prescription pattern before and after the commencement of the study will be analyzed.

All analysis will be tested with a two-sided alpha level of 0.05. For the missing data, the reasons why the data is missing will be analyzed, and multiple imputation will be used.

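### For the binary outcomes, dampness syndrome is analysed by a chi-square test and a trend test with no named covariates, so baseline severity could appear as a dose-response

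*Protocol article*

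**What the plan says.** The Secondary Aims section of the protocol article includes: "To investigate the relationship between population characteristics including Chinese medicine syndromes and tongue features in IMN patients and clinical outcomes".

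Data Collection and Management defines the exposure in two ways from one 30-item scale, with each item scored 0 to 4 and a total of 0 to 120. The binary form is: "More than 15 items with at least one point can be defined as dampness syndrome". The graded form is: "The higher the score, the more severe the dampness syndrome".

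The Statistical Plan gives one sentence on how syndromes are to be analysed: "besides Chi-square test between groups of patients with and without dampness syndrome, a trend test will be performed to assess the dose-response relationship". It names no covariates for either test.

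Three other statements bear on the point:

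- On binary outcomes in general: "Outcomes of composite remission, CR, PR, no response, death, relapse, and composite endpoint will be analysed by using Chi-square test and logistic regression". No covariates are listed for the logistic model, and it is not tied to dampness.
- The Cox model for time to remission is fitted "adjusting for gender, age, baseline proteinuria, GFR, PLA2R antibody level, uric acid, Chinese medicine syndrome, and propensity score".
- The propensity score has this purpose: "Attempting to ensure equivalence in baseline characteristics of participants between the CHM group and the conventional therapy group".

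Eligibility Criteria describes the population: "Eligible candidates for the study are IMN patients of any risk levels to capture a broad spectrum of clinical presentations".

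**The concern.** Dampness is measured as a symptom burden. In a cohort that takes every risk level and mixes newly diagnosed with already treated patients, those with more severe disease may well score higher and also remit less often. A crude comparison by dampness, or a crude trend across dampness levels, would then pick up severity.

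Calling the trend a dose-response invites the reader to take dampness as an independent prognostic factor. Two chi-square-type tests cannot support that reading. At stake is the answer to a named secondary aim on the binary outcomes, which include the primary outcome measure of composite remission at 24 months.

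**Working it through.** **Which stated method handles severity when dampness is the exposure?**

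| Stated method | Outcomes | Severity covariates named? | Dampness as the exposure? |
|---|---|---|---|
| Chi-square, dampness yes/no | binary | none possible | yes |
| Trend test | clinical outcomes | none named | yes |
| Logistic regression | binary | none named | not stated |
| Cox model | time to remission | proteinuria, GFR, PLA2R antibody level, uric acid | no; syndrome is an adjustment covariate |
| Propensity score matching and weighting | CHM v conventional comparison | yes | no; it models CHM exposure |

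No row combines a binary outcome, dampness as the exposure and named severity covariates.

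**Size, two-stratum illustration.** The plan gives no figure on this point to reproduce. From the Sample Size section: 2000 patients with 10% loss, so 2000 × 0.90 = 1,800 evaluable. Assumed: half severe and half mild; remission 55% (severe) and 80% (mild); no dampness effect within either stratum. Overall remission is 0.5 × 0.55 + 0.5 × 0.80 = 67.5%, inside the range of the two rates cited under Sample Size (67.0% and 73.7%).

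Let *a* and *b* be the proportions with dampness among severe and mild patients. With equal strata:

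- remission with dampness = (0.55*a* + 0.80*b*) / (*a* + *b*)
- remission without = [0.55(1 − *a*) + 0.80(1 − *b*)] / (2 − *a* − *b*)

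For *a* = 0.60, *b* = 0.40:

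- with dampness: 0.33 + 0.32 = 0.65; without: 0.22 + 0.48 = 0.70
- odds ratio: (0.65/0.35) / (0.70/0.30) = 1.857/2.333 = 0.80
- 900 patients per group; standard error √[(0.65 × 0.35 + 0.70 × 0.30)/900] = 0.0220
- z = 0.05/0.0220 ≈ 2.27; rejection probability ≈ Φ(2.27 − 1.96) ≈ 62%

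| Dampness in severe v mild | Crude remission, with v without | Odds ratio | Chi-square rejects |
|---|---|---|---|
| 50% v 50% | 67.5% v 67.5% | 1.00 | 5% |
| 55% v 45% | 66.25% v 68.75% | 0.89 | about 20% |
| 60% v 40% | 65% v 70% | 0.80 | about 62% |
| 70% v 35% | 63.3% v 72.1% | 0.67 | about 98% |

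**Size, simulation for the trend test.** Set-up: 1,000 runs of 1,800 patients, remission about 70%, dampness in four equal groups (chi-square at the median split), no dampness effect given severity. The correlation between dampness and severity, and the severity odds ratio per standard deviation (SD), are both assumed.

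| Correlation | Odds ratio per SD | Chi-square rejects | Crude trend rejects | Severity-adjusted logistic trend rejects |
|---|---|---|---|---|
| 0 | 1.3 / 1.5 / 2.0 | 4% / 4% / 5% | 5% / 4% / 5% | 5% / 5% / 5% |
| 0.2 | 1.3 / 1.5 / 2.0 | 13% / 21% / 49% | 17% / 28% / 61% | 5% / 5% / 4% |
| 0.3 | 1.3 / 1.5 / 2.0 | 23% / 46% / 85% | 27% / 57% / 94% | 5% / 5% / 4% |

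At correlation 0.2 and odds ratio 1.5, mean remission falls across the four groups as 72.2%, 70.8%, 69.7% and 68.2%. That looks like a graded response although dampness itself has none.

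**The case against.** Several counter-arguments have force.

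- **Not every dampness analysis is crude.** A reader might infer that severity is ignored throughout. The documents do not support that: the Cox model estimates syndrome jointly with proteinuria, GFR, PLA2R antibody level and uric acid. This limits the point to the binary outcomes.
- **The trend test is nowhere called unadjusted.** The plan lists logistic regression for binary outcomes, and an ordered term in such a model is a trend test. The covariate list may sit in a fuller document. This stands in part: for the trend test, lack of adjustment is an inference from the wording; for the chi-square it is certain. But the article gives a sentence specific to syndromes that names two methods and does not invoke the regression. That is a stated choice of method, not only an omitted detail.
- **The 62% is not a type I error of the chi-square test.** In the illustration the marginal difference of 65% v 70% is real, and the test detects it correctly. This stands. The figure shows how often the crude test would be significant when dampness has no effect at a given severity.
- **The aim speaks only of a relationship.** A crude association is a legitimate, limited answer to that. It is the dose-response language that claims more.
- **Dampness might be thought to steer patients to CHM rather than conventional therapy.** The Introduction says only that CHM prescriptions are individualised by syndrome differentiation or state of illness. It does not say that dampness decides between the two.

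**Conclusion.** The point holds for the binary outcomes. As written, a secondary aim is to be answered by a test that cannot adjust and a trend test with no named covariates, and no stated balancing step addresses dampness groups.

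Whether bias arises depends on a dampness-severity correlation that the documents do not report. With none, the tests keep their nominal level. With assumed correlations of 0.2 to 0.3, the crude trend test is significant in 17% to 94% of simulated studies without any independent dampness effect, against 4% to 5% for the severity-adjusted trend.

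It would go too far to say that confounding has been shown, or that time to remission is affected in the same way. This is a matter of analysis choice for a secondary aim and should be corrected. It does not touch the comparison of CHM with conventional therapy.

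**What to change.** For composite remission and the other binary outcomes, make the main dampness analysis a logistic regression with the dampness score, or prespecified ordered categories of it, as the trend term. Adjust for the baseline covariates already listed for the Cox model (age, gender, proteinuria, GFR, PLA2R antibody level, uric acid), plus serum albumin and incident or prevalent status.

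Add treatment regimen only in a sensitivity analysis. It may lie downstream of dampness, and adjusting for it in the main model could remove part of the association of interest.

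Keep the chi-square and crude trend tests, label them descriptive, and do not call the crude trend a dose-response.

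The cost is a sentence or two in the plan, one more regression model and somewhat wider intervals. The covariates are already in the planned data collection.

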### Outcomes

The primary outcome is clinical composite remission at 24 months after enrollment. Composite remission is defined as either complete remission (CR) or partial remission (PR). Secondary outcomes are CR, PR, time to remission (CR, PR, and CR or PR), no response, relapse, urine protein excretion, urinary protein creatinine ratio, serum albumin, annual change of GFR (GFR slope), PLA2R, adverse events, and composite endpoint of 40% reduction of GFR, doubling of serum creatinine, end-stage renal disease (ESRD), and death. The outcome variables and definitions are presented in Table 1.

**TABLE 1 T1:** Outcome variables and definitions.

Outcome variables	Definitions
Primary outcome	
Composite remission	Either complete remission or partial remission
Secondary outcomes	
Complete remission (CR)	A reduction of proteinuria to ≤0.3g/24 h accompanied by a normal serum albumin and a normal Scr. Beck et al. (2013)
Partial remission (PR)	At least 50% reduction from peak value of proteinuria to a level between 0.3 and 3.5 g/24 h, accompanied by an improvement or normalization of serum albumin and a stable Scr. Beck et al. (2013)
Relapse	The development of proteinuria ≥3.5 g/24 h after a CR or PR
Time to complete remission	Days from enrollment to CR
Time to partial remission	Days from enrollment to PR
No response	No reduction in proteinuria of at least 25% from baseline
Serum albumin	/
Urine protein excretion	Urine protein excretion within 24 h
Urinary protein-to-creatinine ratio (UPCR)	/
Antibodies against PLA2R	/
Doubling of serum creatinine	Doubling increase of serum creatinine from baseline
40% reduction of eGFR	A reduction in eGFR of 40% from baseline. Serum creatinine based eGFR is calculated using the Chronic Kidney disease Epidemiology Collaboration (CKD-EPI) equation
End-stage renal disease (ESRD)	eGFR ≤15 ml/min/1.73m^2^ or commencement of renal replacement treatment
Composite endpoint	ESRD or 40% reduction of eGFR or doubling of serum creatinine
eGFR slope	Annual change in eGFR

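### Dropping incident patients with an early creatinine rise removes early kidney events from the ESRD, 40% eGFR-reduction and slope analyses, and can favour the more nephrotoxic regimen

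*Protocol article*

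**What the plan says.** In the protocol article, the Statistical Plan gives the aim of the rule as "To eliminate the acute effect". It then states that "incident patients who experience a serum creatinine increase of more than 30% within 12 weeks after initiated treatments will be excluded", and limits this to exclusion "in analyses on endpoints in terms of ESRD, 40% eGFR reduction, and eGFR slope". The rule does not ask whether the rise is reversible or confirmed, and it does not reset the baseline. No companion analysis that keeps these patients is described. The one eGFR sensitivity analysis mentioned concerns the 2021 equation.

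Table 1, under Outcomes, defines the endpoints without any exemption for the first 12 weeks. The 40% endpoint is "A reduction in eGFR of 40% from baseline. Serum creatinine based eGFR is calculated using the Chronic Kidney disease Epidemiology Collaboration (CKD-EPI) equation". ESRD is "eGFR ≤15 ml/min/1.73m^2^ or commencement of renal replacement treatment". Doubling of creatinine is "Doubling increase of serum creatinine from baseline". Doubling, the composite endpoint, death and adverse events are also outcomes, and the exclusion sentence names none of them.

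The comparison is between CHM-exposed patients and patients on conventional drugs alone. Baseline differences are handled by propensity-score matching, with inverse probability weighting as a robustness check: "Attempting to ensure equivalence in baseline characteristics of participants between the CHM group and the conventional therapy group".

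**The concern.** Under Enrollment and Follow-Up, incident patients are those newly diagnosed and starting their first treatment, so the 12-week window is time on treatment. Removing patients for what their creatinine does in that window conditions the comparison on a consequence of treatment, and that consequence is a milder form of the endpoint being analysed. It also works in one direction, because only rises lead to removal.

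The Introduction itself notes toxic effects of the conventional regimens, so unequal early kidney injury between groups is plausible, in either direction. If it occurs, the regimen that injures more kidneys early loses more of its worst patients from these three analyses. Matching or weighting on baseline covariates cannot restore them, because the selection happens after baseline.

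**Working it through.** The documents give no figure for how many patients the rule removes, so there is nothing to reproduce. Two checks apply.

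**1. Does the trigger contain the endpoint?**

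The article names the CKD-EPI equation but does not print it. Assume that, with age and sex fixed, eGFR is proportional to creatinine^(−b), with b between 1.0 and 1.5. Assume also that the 30% rise is counted from the same baseline as the endpoints.

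- eGFR fall at a 30% creatinine rise: 1 − 1.3^(−b)
- Creatinine ratio for a 40% eGFR fall: (1/0.6)^(1/b)
- Highest baseline eGFR that can reach 15 without passing a 30% rise: 15 × 1.3^b

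| b | eGFR fall at +30% | Creatinine rise for a 40% fall | Highest baseline eGFR escaping |
|---|---|---|---|
| 1.0 | 23% | 67% | 19.5 |
| 1.2 | 27% | 53% | 20.6 |
| 1.5 | 33% | 41% | 22.2 |

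A 40% fall could avoid the trigger only if b were at least ln(1/0.6)/ln(1.3) = 1.95. A smaller b needs a larger rise. So across the assumed range every 40% event in an incident patient in the first 12 weeks meets the exclusion, and the count in that window is zero by construction.

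Eligibility requires a GFR of at least 15. Early eGFR-defined ESRD therefore escapes only from a baseline of about 15 up to 19.5–22. Because whole patients are removed, their events after week 12 go too.

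A doubling of creatinine in the window (+100%) always meets the trigger and is also a 40% eGFR fall: 1 − 2^(−b) is 50% at b = 1.0 and more above that. On the text, such a patient counts as an event for doubling but is absent from the 40% analysis.

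**2. How large could the bias be? (incident patients only, all inputs assumed)**

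Let e be the proportion with an early rise, r the event risk after a rise, and q the risk otherwise.

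- Risk with everyone kept: e·r + (1 − e)·q
- Risk after exclusion: q

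Take r = 40% and q = 8% in both groups.

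- e = 10%: 0.10 × 0.40 + 0.90 × 0.08 = 0.112
- e = 3%: 0.03 × 0.40 + 0.97 × 0.08 = 0.0896
- Risk ratio with everyone kept: 0.112/0.0896 = 1.25
- Risk ratio after exclusion: 0.08/0.08 = 1.00
- Share of the worse regimen's events deleted: 0.040/0.112 = 36%

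With early rises of 5% v 2% the full ratio is 0.096/0.0864 = 1.11. With 15% v 5% it is 0.128/0.096 = 1.33. The 1.00 after exclusion follows from setting q equal in both groups. In general the rule returns the ratio of the two q values and discards what early injury contributes. If early-rise rates are equal, this model shows no bias in the ratio, only lower absolute risks.

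**Dilution by prevalent patients, who are never excluded (assumed 50% share).**

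- Prevalent patients have no early rises and 8% risk: the full ratio is (0.5 × 0.112 + 0.5 × 0.08)/(0.5 × 0.0896 + 0.5 × 0.08) = 0.096/0.0848 = 1.13. The ratio after exclusion is 1.00, and 0.020/0.096 = 21% of the worse regimen's events are deleted.
- Prevalent patients carry the same overall risks as incident ones: the full ratio is 1.25. After exclusion the risks are (0.45 × 0.08 + 0.5 × 0.112)/0.95 = 0.0968 and (0.485 × 0.08 + 0.5 × 0.0896)/0.985 = 0.0849, a ratio of 1.14.

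**The case against.** The aim of the rule is legitimate. An early creatinine change may be reversible, and separating it from long-term loss matters, above all for slope. Table 1 states no confirmation requirement, so simply keeping everyone would let a transient rise count as a lasting event. This stands, and the remedy has to deal with it. It does not rescue the rule, which drops reversible and permanent injury alike.

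A reader might infer that the study can no longer show nephrotoxicity at all. The text does not support that. Doubling of creatinine, the composite, death and adverse events are outside the exclusion sentence, so early injury may still appear there. What remains is an inconsistency: the same early event could count in the composite and vanish from its own component.

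A reader might also infer that the exclusion is applied after matching and so breaks matched pairs. The article does not state the order, and the weighted analysis has no pairs. Pairs break only if exclusion follows matching. The selection problem is there in either order.

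It is also tempting to say that the rule makes incident and prevalent subgroups non-comparable. Prevalent patients were already on treatment before the study, so the two groups differ by design whatever the filter does.

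**Conclusion.** The concern holds for three secondary analyses: ESRD, 40% eGFR reduction and eGFR slope. The deletion of 40% events in the first 12 weeks among incident patients follows from the definitions for any exponent below about 1.95. The direction of bias, towards the more nephrotoxic regimen, depends on regimens differing in early injury, which the documents do not show.

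The size is illustrative only. In incident patients a true ratio of 1.11 to 1.33 becomes 1.00 under the assumed inputs, with equal risk among those without a rise. In the whole cohort the distortion shrinks with the share of prevalent patients. The 1.25-to-1.00 contrast should not be read as a whole-cohort estimate.

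Nor should a reader infer that the main result is compromised. The primary outcome is composite remission at 24 months, and the exclusion does not apply to it. The rule should be changed, but it does not undermine the study's principal analysis.

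**What to change.** Rewrite the exclusion sentence in the Statistical Plan as follows.

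- Keep all patients in the main analyses of ESRD, 40% eGFR reduction and eGFR slope.
- Handle the acute phase directly: require the 40% fall to be confirmed at a later scheduled measurement, and fit a two-phase slope model (acute, then chronic).
- Report the proportion with a creatinine rise above 30% within 12 weeks, by regimen, as a safety outcome. The month-3 visit may be remote, so give the number with a creatinine value in the window as the denominator.
- Keep the present exclusion only as a labelled sensitivity analysis, with the numbers excluded by group.
- State that the composite and its components use the same patients.

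The cost is a few sentences in the plan and no new data collection. The downside is that some reversible early rises may count as events where no later measurement is available.
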